### Treatment Period - Early Completion

Once a wound has been judged to be completely healed (defined as 100% epithelialisation with no presence of exudate or scab), participants will be referred for correct fitting of long-term compression hosiery to prevent recurrence of venous ulceration. Participants will also receive an education pamphlet as a resource on how best to prevent recurrence. Participants will proceed to the Follow-Up Period and will be followed up monthly for 3 months.

### Follow-Up Period - Month 1, 2 and 3

Participants whose target ulcer have been judged to be completely healed by/at 12 weeks of treatment will need to attend the outpatient department at the treating hospital to be assessed monthly (± 2 days) for 3 consecutive months during the Follow-Up Period to monitor safety and recurrence rates. If this is not possible the participants will be phoned at these intervals and asked about recurrence.

At each follow up visit the participant will have the following assessments performed:

◦ Check whether the wound remains healed.

◦ If the target ulcer has recurred ascertain:

- Date of recurrence

- Target Ulcer Assessment

- Determine if study participant has continued with compression hosiery treatment. If yes, assess tolerability of compression hosiery (very comfortable, comfortable, uncomfortable, and very uncomfortable). If no; reason why.

◦ Adverse Events. Any untoward medical occurrence in a trial participant even if it does not necessarily have a causal relationship with the treatment.

◦ Ulcer treatment - Participants will be referred to wound clinic care if the ulcer has not healed or has recurred in the follow up period.

◦ SF 36 and CWIS Quality of Life (Month 3 only).

Study participants whose ulcers have not healed by/at the 12 week visit will be released from the study into the care of a wound clinic. All care will be made to ensure that all adverse events are followed until resolution. Study schedule outlined in Table 1.

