#### Secondary Outcomes

1. The proportion of ulcers healed within the trial period. (Complete healing is defined as full 100% epithelialisation or skin closure without drainage)

2. The incidence of treatment related adverse events

3. Reliability and acceptability (withdrawals)

4. Number of adverse effects and serious adverse events

5. Quality of Life measures at baseline, at end of treatment and at 3 month follow up (SF 36 and Cardiff Wound Impact Schedule (CWIS))

6. Self-reported compliance of compression bandage

7. Recurrence rates.

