### Screening Evaluation

The screening period will last for one week during which time study participants will be required to wear compression bandages as randomised. Prospective participants will be informed about all aspects of the clinical study, including procedures, risks and benefits. Receipt of this information will be acknowledged for each study participant through the provision of written informed consent by the participant. A copy of the information sheet and consent form will be provided to each participant.

The following screening assessments will be conducted for each potential participant:

Informed consent; assessment of compliance with the inclusion and exclusion criteria; patient medical history; concomitant medications and treatments; physical examination and target ulcer assessment.

### Treatment Period - Day 1

Participants will be bandaged according to their random number allocation. The intact standard compression bandage should be removed and the target ulcer and limb thoroughly cleansed with tap water and soap-free wash. The wound may be debrided if deemed clinically necessary as sloughy and exudative wounds with unhealthy wound beds will take longer to heal. Wound debridement and exudate management is important in early stages to ensure adequate wound bed preparation.

The following assessments will be conducted for each participant: Target Ulcer Assessment, Temperature, pulse and blood pressure, intercurrent illness and medication, SF 36 and CWIS Quality of Life, Adverse Events and confirmation of next visit (7 days time).

### Treatment Period - Weeks 1 to 12

Participants will return to the study centre weekly following Day 1 for the following assessments: Check whether the wound has healed, Target Ulcer Assessment, Assessment of tolerability of product (very comfortable, comfortable, uncomfortable, very uncomfortable), Temperature, pulse and blood pressure, intercurrent illness and medication, Adverse Events, SF 36 and CWIS Quality of Life (Week 12 only)

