### Duration of Treatment Including Follow-Up

The ulcer will be dressed weekly with standard compression bandage for one week run in period. The treatment period is 12 weeks duration. All participants will be seen on a weekly basis by an experienced leg ulcer practitioner. Additional visits may be necessary if clinically indicated. Study participants randomised to the intervention group will be treated with graduated three layer straight tubular bandage system once per week for 12 weeks. Study participants randomised to the control group will be treated with standard compression bandage for 12 weeks.

Study participants whose ulcers heal before or at 12 weeks of treatment will be assessed monthly for 3 consecutive months during the Follow-Up Period to monitor for safety and target ulcer recurrence rates. Study participants whose ulcers have not healed at the 12 week visit will be released from the study and returned to the care of the speciality wound clinic. All care will be made to ensure that all adverse events are followed until resolution.

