#### SF36 and CWIS Quality of Life

Participants will be asked to complete the SF36 and CWIS Quality of Life surveys at screening visit and at completion of study treatment. A copy will be retained in the CRF.

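### Month-3 quality of life is scheduled only for participants whose ulcer healed, so it cannot be compared between the arms as randomised; and the text does not settle whether early healers are assessed at week 12

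*Protocol article*

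**What the plan says.** All references are to the protocol article.

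- **Outcome list.** Secondary Outcomes includes "Quality of Life measures at baseline, at end of treatment and at 3 month follow up" and, as a separate item, "Recurrence rates". Neither is limited to healed participants.
- **Who is followed to month 3.** The section on the three monthly follow-up visits sets the entry rule: "Participants whose target ulcer have been judged to be completely healed by/at 12 weeks of treatment will need to attend the outpatient department". Its closing paragraph deals with everyone else: "Study participants whose ulcers have not healed by/at the 12 week visit will be released from the study into the care of a wound clinic". The section on treatment duration repeats this: "Study participants whose ulcers have not healed at the 12 week visit will be released from the study and returned to the care". Only adverse events are pursued further. The month-3 questionnaires appear only in the follow-up visit list and in the follow-up columns of Table 1.
- **Participants who heal early.** Treatment Period - Early Completion: "Participants will proceed to the Follow-Up Period and will be followed up monthly for 3 months". Plan and Trial Design instead describes weekly review across the 12-week treatment period, with monthly review as an addition in a later period for those who heal. Duration of Treatment has all participants seen weekly. Table 1 puts the questionnaires and the target ulcer assessment at week 12 with no restriction to unhealed ulcers.
- **Questionnaire timing.** Treatment Period - Weeks 1 to 12 and Table 1 place the on-treatment questionnaire at week 12 only, and Treatment Period - Day 1 and Table 1 place the baseline one at Day 1. SF36 and CWIS Quality of Life has the "surveys at screening visit and at completion of study treatment", and does not mention month 3.

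**The concern.** A comparison of month-3 scores between arms would be a comparison of healers with healers. If one arm heals more ulcers, its healers are a less selected group, and randomisation no longer protects the contrast. A real quality-of-life benefit that works through healing can disappear, and a difference can appear where none exists. A statistical analysis plan could label or model these data, but it could not recover questionnaires that the visit schedule never collects.

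The timing conflicts bear on the one quality-of-life comparison that could be made in everyone randomised, at week 12. If early healers answer at healing, or not at all, while the others answer at week 12, that comparison also loses its common time point. The two baseline times are a week apart, with compression already worn in between.

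The article says the pilot will inform the design of a larger trial, so the schedule could be carried forward.

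**Working it through.** **1. The plan's own figures** (Sample Size and Analysis plan).
- Log-scale difference: ln(0.8/0.5) = 0.470.
- n per group = 2 × (1.96 + 0.842)² × 0.5² / 0.47² = 17.8, so 18, as stated.
- Allowing for 20% loss: 18/0.80 = 22.5, so 23 per arm and 46 in total, as stated.
- Power for healing, 20% v 60%, 18 per group: 56.5% by a continuity-corrected z-test, within 2 points of the stated 55% (61.4% by Fisher's exact test, 70.4% by the uncorrected z-test).

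The 20% and 60% are thus the plan's planning rates, and are used below only to count who could have month-3 data.

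**2. Eligible for month-3 questionnaires.**

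| Base per arm | 3L (20%) | Standard (60%) | Total |
|---|---|---|---|
| 23 randomised | 4.6 | 13.8 | 18.4 of 46 |
| 18 evaluable | 3.6 | 10.8 | 14.4 of 36 |

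Of those randomised, 46 − 18.4 = 27.6 would have no month-3 questionnaire by design: 80% of one arm and 40% of the other. With the 25% to 70% healing at 12 weeks spanned by the Background section, applied overall, 11.5 to 32.2 of 46 would be eligible. Actual numbers could be lower, since the telephone substitute for a follow-up visit asks only about recurrence.

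**3. What selection could do (illustrations on assumptions; the documents give no quality-of-life figures).**
- *Hiding a difference.* Assume healed participants score 20 points better and nothing else matters. The randomised difference is (0.60 − 0.20) × 20 = 8 points; the healed-only difference is 0.
- *Creating one.* Assume no treatment effect on quality of life, a correlation ρ between quality of life and a normally distributed propensity to heal, and healing in the top 20% v the top 60%. Mean propensity among healers is φ(0.842)/0.20 = 1.400 v φ(−0.253)/0.60 = 0.644, a gap of 0.756. The healed-only difference is 0.756ρ SD: 0.15 at ρ = 0.2, 0.23 at 0.3, 0.38 at 0.5 and 0.53 at 0.7, favouring the arm with fewer healers.
- *Precision.* For an assumed true difference of 0.8 SD, power is Φ(0.8/√(1/18 + 1/18) − 1.96) = 67% with 18 v 18, and Φ(0.8/√(1/4 + 1/11) − 1.96) = 28% with 4 v 11.

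**4. Month 3 is not a fixed time since randomisation.** If follow-up starts at healing, three months (about 13 weeks) falls at about week 17 for healing at week 4 and week 25 for healing at week 12.

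**5. The timing sections side by side.**

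| Question | One reading | Other reading |
|---|---|---|
| Do early healers attend week 12? | Yes: Plan and Trial Design, Duration of Treatment, Table 1 | They move on at healing: Early Completion |
| Post-treatment questionnaire | Week 12: Weeks 1 to 12, Table 1 | Completion of treatment: SF36 and CWIS section |
| Baseline questionnaire | Day 1: Day 1 section, Table 1 | Screening: SF36 and CWIS section |

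**The case against.** The strongest reply has four parts.

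*Early healers may well be seen at week 12.* A reader of Early Completion might infer that they certainly leave the schedule, and hence that no quality-of-life comparison at a common time exists. The documents do not support that as fact, because three places point the other way. What stands is an unresolved conflict: week-12 data in early healers are not assured.

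*The primary endpoint is largely protected.* A reader might infer that an ulcer healing in week 3 and recurring by week 12 would be scored as healed. Nothing in the text says so. The outcome is defined at week 12, and follow-up visits check whether the wound remains healed and, if it has recurred, record the date and repeat the ulcer assessment. For healing at week 3, monthly visits would fall near weeks 7, 12 and 16. What remains is that the area may be measured somewhat off week 12 in an early healer who recurs.

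*Recurrence is not wrongly restricted.* Only a healed ulcer can recur, so following healers is inherent. The denominator matters only if recurrence is compared between arms.

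*No between-arm test of month-3 quality of life is specified, and this is a pilot.* That is correct, and a descriptive label would meet the point. But the outcome is listed for the trial as a whole, with no sign that it exists only for healers.

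The 20% and 60% are also a power scenario, not a forecast.

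**Conclusion.** The point holds for month-3 SF-36 and CWIS: as scheduled, they are observed only in participants selected by a post-randomisation outcome that the plan's power statement assumes to differ threefold between arms. On those rates about 5 v 14 of 23 per arm are eligible. If healing were similar in the arms the counts would be closer and the distortion probably smaller, but the comparison would still not be one of randomised groups. The 8-point and 0.15 to 0.53 SD figures show mechanism and direction under stated assumptions; they are not estimates for this trial.

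For week 12 the conclusion is narrower. The sections contradict one another on early healers and on both questionnaire times, so a common-time comparison and a week-12 ulcer status are not assured for early healers. The effect on the primary endpoint is confined to early healers whose ulcer recurs before week 12. As mainly secondary outcomes of a pilot are affected, this should be corrected but does not undermine the trial's main purpose.

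**What to change.** 1. State that every randomised participant, early healers included, completes SF-36 and CWIS and has target-ulcer status (area if recurred) assessed in person at 12 weeks after Day 1. A telephone call cannot supply an area, and the nearest monthly visit does not give a common time.
2. Use that week-12 status for the primary endpoint, and make week 12 the between-arm quality-of-life comparison.
3. Report month-3 quality of life as descriptive among healed participants.
4. If recurrence is compared between arms, report the proportion healed and still healed, with all randomised as denominator.
5. Reconcile Plan and Trial Design, the treatment and follow-up visit sections, Duration of Treatment, the SF36 and CWIS section and Table 1, with a single baseline questionnaire time.

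The cost is about one extra visit and questionnaire per early healer. The plan already asks participants who drop out to return at 12 weeks for ulcer measurement, so the principle is not new. With 25 participants recruited and 12 of them healed when the article was written, the change can reach only those who have not yet passed week 12; the others should be reported as having no assured assessment at that time.

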### Duration of Treatment Including Follow-Up

The ulcer will be dressed weekly with standard compression bandage for one week run in period. The treatment period is 12 weeks duration. All participants will be seen on a weekly basis by an experienced leg ulcer practitioner. Additional visits may be necessary if clinically indicated. Study participants randomised to the intervention group will be treated with graduated three layer straight tubular bandage system once per week for 12 weeks. Study participants randomised to the control group will be treated with standard compression bandage for 12 weeks.

Study participants whose ulcers heal before or at 12 weeks of treatment will be assessed monthly for 3 consecutive months during the Follow-Up Period to monitor for safety and target ulcer recurrence rates. Study participants whose ulcers have not healed at the 12 week visit will be released from the study and returned to the care of the speciality wound clinic. All care will be made to ensure that all adverse events are followed until resolution.

### Assessment Procedures

#### Physical Examination

A physical assessment of the participant will include demographics (gender, date of birth, height, weight, smoking and alcohol history), vascular assessment taking particular note of any signs and symptoms of chronic venous insufficiency, ankle mobility, vital signs (temperature, pulse and supine blood pressure) and Ankle-Brachial Index to assess the arterial supply of the target limb. This is a non-invasive procedure that involves measuring blood pressure on the foot and on the arm and is necessary prior to application of any compression bandage to exclude arterial disease. Participants will not be included in the trial if they have an Ankle Brachial index of less than 0.8.

#### Target Ulcer Assessment

The target ulcer should be identified from the entrance criteria (i.e. largest ulcer on limb and separated from other ulcers by at least 2 cm).

##### Visitrak wound tracing

The ulcer outline will be traced and the ulcer area calculated to determine ulcer size

##### Digital photo of ulcer

The ulcer will be photographed using a digital camera and image saved and sent to an independent assessor who will be blinded to treatment assignment. The target ulcer will also be photographed when complete epithelialisation is evident.

##### Percentage of Granulation Tissue

The ulcer will be assessed for quality of wound bed tissue (red <25%, red 25%-50%, red 50%-75%, >75%, hypergranulated, other).

##### Depth

The ulcer will be assessed for depth with Visitrak probe (Grade I, II, III, IV).

##### Surrounding Skin

The condition of the surrounding skin will be assessed (normal, dry, wet eczema, dry eczema, erythema, other).

##### Exudate level

The level of exudate will be assessed (copious, medium, minimal, nil).

#### SF36 and CWIS Quality of Life

Participants will be asked to complete the SF36 and CWIS Quality of Life surveys at screening visit and at completion of study treatment. A copy will be retained in the CRF.

### Statistical Methodology

Statistical summaries and analyses of data will be performed at Monash University.

### Sample Size and Analysis plan

Participants will be randomised to graduated three layer straight tubular bandaging system (3L) or to a standard short stretch compression bandaging system. From a previous study [25] we anticipate an average reduction of 20% in wound size from baseline to follow-up in the group that receives 3L. To detect with 80% power a difference in the mean percentage reduction of 50% in the group with standard compression versus 20% in the 3L group requires 18 participants per group. This assumes a two-sided z-test (alpha = 0.05) of mean log (Area2/Area1) where Area2 is the area of the wound at follow-up and Area1 is the area of the wound at baseline. Percentage reduction is defined as 100(Area2-Area1)/Area1 and percentage reductions of 20% and 50% correspond to a difference in means of 0.47 on the scale of analysis (log(Area2/Area1)). From a previous study (Vowden et al, 2007) we estimate the standard deviation of log(Area2/Area1) to be 0.5 in each group. If a wound has completely healed and Area2 = 0 then we will use log (min (Area2)/Area1) in analysis where Area2 = Area1/100 is the smallest observed wound area at follow-up among those participants whose wounds did not completely heal. A two-sided p-value of 0.05 will be considered to be statistically significant.

With 18 participants per group the study will have 55% power to address the secondary endpoint of complete healing if the effect of standard compression is to improve the rate of healing from 20% of participants fully healed (with 3L) to 60% with standard compression.

The analysis of the primary endpoint will be by z-test and linear regression if the distribution of log (A2/A1) is reasonably symmetric. It is unclear from previous studies whether this will be the case. If necessary the analysis of hypothesis 1 will be by non-parametric Wilcoxon rank-sum test. If major differences are evident in key variables (age, gender, ethnicity, BMI, smoking, ABPI, ankle and calf circumference, range of ankle mobility, past medical history- diabetes, anaemia, hypertension, past surgical history-hip surgery, venous surgery/ligation, DVT, medication history) between allocated groups at baseline, then the baseline values will be included as covariates in a second linear regression model for the primary outcome. Imbalance will be defined as a difference in means (on a log scale for variables following a skewed distribution) of ≥ 0.33 standard deviations or, for binary and categorical variables a relative risk of ≥ 2 (where prevalence is ≥ 10%).

Finally, 18 participants per group need to have wound area assessed at the end of the 12-week follow-up. To allow for loss-to-follow-up of 20% of participants between baseline and follow-up we will randomise 23 participants to each arm.

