#### Primary Outcome

The percentage reduction of wound area from baseline compared to week 12 following randomisation. The size of the wound area will be measured by Visitrak wound measurement system and wound digital photographs.

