### Pilot study sample size justification

We will recruit 46 participants in total to enable the estimation of the between-person variability in percentage reduction in wound size from baseline to 12 weeks. There are insufficient previous studies to ascertain a likely value for this variability for use in power calculations for a fully powered trial.

The analysis principle for the primary outcome will be Intention-to-treat. The data will be analysed according to the treatment group to which participants are randomised even if they do not comply fully with their treatment. If participants drop out of the study they will be asked if they would still be prepared to return at the 12 week end of treatment schedule for target ulcer measurement.

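### The primary-analysis score for a healed ulcer is defined in two incompatible ways, and under one of them a healed small ulcer can score worse than an unhealed large one

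*Protocol article*

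**What the plan says.** The Primary Outcome section names "The percentage reduction of wound area from baseline compared to week 12 following randomisation". The Sample Size and Analysis plan section analyses this as log(Area2/Area1) and sizes the trial for a difference of 0.47 on that scale. For the spread it says "we estimate the standard deviation of log(Area2/Area1) to be 0.5 in each group".

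A healed ulcer has Area2 = 0, so the log needs a substitute. The rule is: "we will use log (min (Area2)/Area1) in analysis where Area2 = Area1/100 is the smallest observed wound area at follow-up", where the minimum is taken over participants whose ulcers did not heal.

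The analysis is a z-test and linear regression if the log ratio is reasonably symmetric, with the Wilcoxon rank-sum test otherwise. The same section gives planning rates for complete healing of 20% (3L) and 60% (standard compression). It also states: "Percentage reduction is defined as 100(Area2-Area1)/Area1".

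**The concern.** One sentence gives two different substitutes. Area1/100 is specific to the participant and fixes the ratio. The smallest residual area is common to the sample and fixes the area, so the ratio varies with baseline. Nothing else in the article reconciles them.

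Under the fixed-area half, the order of outcomes can reverse: complete healing of a small ulcer can count as a poorer result than partial healing of a large one. Under the fixed-ratio half, the order is sound except against an unhealed ulcer that shrinks by more than 99%, but the mean and SD depend heavily on the divisor of 100, which is not justified.

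Healed ulcers will not be rare. Beyond the planning rates, the Current study status section already reports 12 healed participants, with 25 recruited. That is not a 12-week healing rate, because the 25 are recruits rather than completers. Still, it shows that the rule will govern much of the primary data. In an open-label trial, two primary results would be open to choice after the data are seen.

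**Working it through.** **The plan's own figure.** Effect: ln(0.8) - ln(0.5) = 0.470. With SD 0.5, two-sided alpha 0.05 and 80% power, n = 2(1.960 + 0.842)² × 0.5²/0.47² = 17.8, so 18 per group. Then 18/0.8 = 22.5, so 23 per arm. The stated 18 and 23 reproduce, but with an SD of 0.5, which leaves no room for the healed-ulcer scores (see below).

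**The two readings.** Eligible baselines are 1 to 20 cm2 (Inclusion Criteria).

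- Fixed ratio: the substitute area is 0.01 to 0.20 cm2, and the score is ln(0.01) = -4.61 for everyone.
- Fixed area m: the score is ln(m/Area1).

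They agree only for a healed ulcer with baseline 100m. With m = 0.3 cm2 that baseline would be 30 cm2, outside the eligible range.

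**Reversal under the fixed-area reading.** A healed ulcer scores worse than an unhealed one whenever its m/Area1 exceeds the other's Area2/Area1.

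| m (cm2) | Healed 1 cm2 | Healed 20 cm2 | Unhealed 20 cm2 ulcer beats healed 1 cm2 if it ends below |
|---|---|---|---|
| 0.1 | -2.30 | -5.30 | 2 cm2 |
| 0.2 | -1.61 | -4.61 | 4 cm2 |
| 0.5 | -0.69 | -3.69 | 10 cm2 |

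With m = 0.3, a healed 1 cm2 ulcer scores ln(0.3) = -1.20, and a 20 cm2 ulcer reduced to 2 cm2 scores ln(0.1) = -2.30. Whatever m is, healed ulcers of 1 and 20 cm2 differ by ln 20 = 3.00, over six times the target effect of 0.47.

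**Effect on the SD, fixed-ratio reading.** For a proportion p healed and an unhealed mean μ with SD 0.5, the variance is (1-p)0.25 + p(1-p)(-4.605-μ)².

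- 3L, p = 0.2, μ = ln 0.8: √(0.20 + 0.16 × 4.382²) = 1.81.
- Standard compression, p = 0.6, μ = ln 0.5: √(0.10 + 0.24 × 3.912²) = 1.94.

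The arm means are -1.10 and -3.04, a difference of 1.94 rather than 0.47.

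**Simulation.** Assumptions: 18 per arm, baselines log-uniform on 1 to 20 cm2, unhealed SD 0.5, 4,000 trials per row. Each cell gives fixed ratio / fixed area.

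| Healed, 3L v standard | Unhealed reduction, 3L v standard | Mean difference | Pooled SD | z-test rejection | Wilcoxon rejection |
|---|---|---|---|---|---|
| 20% v 60% | 35% v 35% | 1.67 / 0.71 | 1.90 / 1.04 | 72% / 52% | 57% / 46% |
| 20% v 60% | 20% v 50% | 1.95 / 0.98 | 1.87 / 1.02 | 85% / 80% | 90% / 85% |
| 40% v 40% | 20% v 50% | 0.29 / 0.27 | 2.07 / 1.12 | 8% / 13% | 16% / 17% |
| 50% v 50% | 35% v 35% | 0 / 0 | 2.12 / 1.10 | 6% / 6% | 5% / 5% |

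A separate simulation of the first scenario with a t-test gave 70% and 51%.

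Under the fixed-area reading, with three assumed baseline distributions, at least one reversal occurred in 80 to 91% of trials, and 17 to 24% of healed ulcers scored worse than some unhealed ulcer. As a share of all healed/unhealed pairs (log-uniform baselines), about 4 to 5% were reversed.

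**Sign.** For a halved wound, 100(0.5 - 1)/1 = -50, so the stated formula returns a negative number for a reduction.

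**The case against.** Substituting the smallest residual is defensible on the area scale: no healed ulcer is given a larger area than an unhealed one, and between ulcers of equal baseline the order is kept. The symmetry condition would probably send such two-humped data to the Wilcoxon test. Under Area1/100 that test ties healed ulcers at the best rank, unless an unhealed ulcer shrinks by more than 99%. Stratification at 10 cm2 limits imbalance between arms in baseline size. All of this stands. It does not settle which half of the sentence applies, and under the fixed-area half the Wilcoxon test ranks the reversed scores.

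A reader might infer more than the documents support:

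- That changing the divisor would change the main trial's sample size by the square of the SD ratio. That holds the effect fixed, whereas the divisor moves effect and SD together. With 20% v 60% healed and unhealed μ = -0.43, 1/100 gives a difference of 1.67 and SD 1.91, so n = 15.7 × (1.91/1.67)² = 20.5 per group. With 1/1000 the figures are 2.59, 2.92 and 20.0. For the same reason, pairing the inflated SDs with 0.47 is not a valid sample size.
- That the SD the pilot is meant to supply is itself distorted. The Pilot study sample size justification says "to enable the estimation of the between-person variability in percentage reduction in wound size from baseline to 12 weeks". On that scale a healed ulcer is simply 100% and needs no substitute. Only the log-scale SD is affected, which matters if the main trial is planned on the log scale.
- That healed small ulcers always rank below unhealed large ones, or that the test is invalid. Reversal is possible and likely somewhere in the sample, but few pairs reverse and type I error stays near 5%.

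**Conclusion.** The point holds as a contradiction in a stated rule for the primary analysis, with possible reversal of outcomes under one of its two readings. Both follow from the text and direct arithmetic, without distributional assumptions. The consequences for the estimate, the log-scale SD and the power are real, but their size depends on the assumed baseline and shrinkage distributions. The power gap is about 20 percentage points for the z-test and 11 for Wilcoxon when the arms differ only in healing, about 5 points for each when unhealed shrinkage also differs as planned, and it reverses direction when only shrinkage differs. The sign error is certain but minor: the analysis uses the log ratio, and 0.47 and 18 per group are unaffected.

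**What to change.** Delete the smallest-area definition and state one rule under which every healed ulcer receives the same, best score. There are two ways to do this:

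1. Keep the log analysis with a single constant ratio fixed in advance, floor any unhealed ratio that falls below it, and add a sensitivity analysis that varies the constant. This keeps the z-test and the covariate-adjusted regression.
2. Tie healed ulcers at the best rank, order unhealed ulcers by Area2/Area1 below them, and use the tie-corrected form of the Wilcoxon test already named. This needs no arbitrary constant. The effect is then rank-based, no longer matches the z-test sample-size basis or the regression, and yields no SD for the main trial.

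Under either option, report the proportion healed, and separately the mean log ratio and SD among unhealed ulcers, so that any log-scale variability carried forward is not set by the substituted value. Define percentage reduction as 100(Area1 - Area2)/Area1. The first option costs a few sentences and one sensitivity analysis. The second also requires the sample-size basis to be restated.

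### The primary z-test with an estimated SD runs at about 5.8% rather than 5%, and the choice between it and Wilcoxon rests on an undefined look at the outcome

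*Protocol article*

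**What the plan says.** All of this stands under Sample Size and Analysis plan in the protocol article.

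- **Planning test.** "This assumes a two-sided z-test (alpha = 0.05) of mean log (Area2/Area1"), with the design said to have 80% power.
- **Planning inputs.** Reductions of 20% and 50% "correspond to a difference in means of 0.47 on the scale of analysis", and "we estimate the standard deviation of log(Area2/Area1) to be 0.5 in each group". This "requires 18 participants per group", raised to 23 randomised per arm for 20% loss.
- **Threshold.** "A two-sided p-value of 0.05 will be considered to be statistically significant".
- **Analysis.** "The analysis of the primary endpoint will be by z-test and linear regression if the distribution of log (A2/A1) is reasonably symmetric". The text adds that earlier studies do not show whether it will be symmetric.
- **Fallback.** "If necessary the analysis of hypothesis 1 will be by non-parametric Wilcoxon rank-sum test".
- **Healed ulcers.** Their follow-up area of zero is replaced before taking logs. The sentence mentions both the smallest unhealed area and one hundredth of the baseline area.

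The section Pilot study sample size justification says that too few studies exist to settle the between-person variability, and that this trial is to estimate it. The Randomisation section withholds the codes from the researchers until recruitment, data collection and wound measurement analysis are complete.

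**The concern.** A z-test with normal critical values is exact only when the SD is known. Here the document itself says the variability is not established, so the SD has to come from the trial's own data. At 18 per group the reference distribution is then t with 34 degrees of freedom, and 1.96 is too small a cut-off.

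The second issue is which test counts. Three procedures are named (z-test, regression, Wilcoxon). The switch depends on how the outcome looks, with no criterion for adequate symmetry and no statement of whether the judgement precedes knowledge of allocation. Because healed ulcers are all moved to an extreme value, a cluster at one end is predictable now. If the tests give different answers on such data, a loosely worded rule can settle the trial's primary result.

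**Working it through.** **Inputs.** From Sample Size and Analysis plan: two-sided alpha 0.05, difference 0.47, SD 0.5, 18 evaluable per group, 20% loss.

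**1. Reproduce the plan's figures.**
- Difference: ln(0.8/0.5) = 0.470.
- n per group = 2 × 0.5² × (1.960 + 0.842)² / 0.47² = 17.77, rounded up to 18. Power of the z-test at 18 is 80.5%.
- 18 / (1 − 0.20) = 22.5, rounded up to 23.

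Both stated sample sizes are correct for a z-test with known SD.

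**2. Error rate with the SD estimated.**
- 18 per group, 34 df: 2 × P(t₃₄ > 1.96) = 5.8%.
- 23 per group, 44 df: 2 × P(t₄₄ > 1.96) = 5.6%.

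**3. Power with the SD estimated.** The noncentrality is 0.47 / (0.5 × √(2/18)) = 2.82.

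| Test at 18 per group | Size | Power, normal data, SD 0.5 |
|---|---|---|
| z, cut-off 1.96, estimated SD | 5.8% | 80.3% |
| t, 34 df | 5.0% | 78.2% |
| Wilcoxon (simulated) | 4.8% | 75.2% |

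The z-test keeps its 80% only by running at 5.8%. A t-test reaches 80.5% at 19 per group.

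**4. Effect of the symmetry switch on the error rate.** The plan gives no trigger, so I assumed residual skewness above 0.5 or above 1.0, judged from residuals about each arm's mean, without reference to the size of the treatment difference (40,000 simulated trials, 18 per arm).
- Normal data: 5.9% to 6.0% switching between z and Wilcoxon; 5.1% to 5.3% switching between t and Wilcoxon.
- Assumed 20% to 50% healed, each set to ln(0.01): 5.0% to 6.3% switching between z and Wilcoxon.

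Most of the excess over 5% comes from the z cut-off, not from the switch.

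**5. How often the tests disagree.** Assumptions: unhealed ulcers normal with SD 0.5 and means 0.47 apart; healed ulcers set to ln(0.01), which is one reading of the replacement rule.

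| Healed (3L / short stretch) | z power | Wilcoxon power | Tests disagree |
|---|---|---|---|
| 20% / 20% | 12% | 37% | about 27% |
| 40% / 40% | 8% | 15% | about 10% |
| 20% / 60% (the plan's healing scenario) | 84% | 89% | about 7% |

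Symmetry is also an unreliable trigger. In the null simulations skewness exceeds 0.5 in 97% of trials at 20% healed, but in only 26% at 40% healed. In the latter case the data form two clumps that can pass as symmetric.

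**The case against.** The strongest reply has four parts.

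- **The sample size is right.** 18 per group follows from the stated inputs, and the planned z-test has 80.3% power even with an estimated SD. This stands. A reader might infer that the stated 80% is an error. It is not: 78.2% belongs to a t-test that the plan does not name, and what fails, by about 2 points, is having 5% and 80% together.
- **The switch hardly inflates error.** This stands for a symmetry check made without allocation. A reader might infer a true error rate near 7% or 8%. Simulation gives 6.4% to 7.8% only if the smaller of the z and Wilcoxon p-values is always taken, and the plan contains no such rule.
- **The criterion may sit in an analysis plan that is not shown, and the codes are withheld until measurement is complete.** This stands in part. A blinded choice is possible, and the absence of a numerical criterion is not in itself the fault. But the article does fix a rule that makes the primary test depend on the outcome, and it does not say the choice comes before the codes are released.
- **Regression, named beside the z-test, normally uses t.** True, but the text does not say which p-value governs.

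One further inference should be avoided. Current study status reports 12 healed among 25 recruited. That is an interim status line, not a 12-week healing proportion: some of the 25 may still be under treatment. It supports expecting a pile-up, not a planning value of 48%.

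**Conclusion.** The concern holds in limited form. Used literally, the z-test has a two-sided size of 5.8% at 18 per group (5.6% at 23) instead of 5%. At a true 5%, power is 78.2% under the plan's own normal model with SD 0.5. These differences are small. They rest on the SD being estimated from the trial data, which follows from the pilot justification but is not stated outright.

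The choice of test matters more. With healed ulcers at an extreme value, z and Wilcoxon can lead to different conclusions, in about 27% of simulated trials in the least favourable case examined. That figure depends on the assumed healing share and replacement value, and falls to about 7% in the plan's own healing scenario. Severity is minor to moderate, because the trial is a pilot meant to inform a larger one.

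**What to change.** Before the allocation codes are released:

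1. Name one primary test. A tie-corrected Wilcoxon rank-sum test with all healed ulcers tied as best is one suitable choice. It does not depend on the replacement value, and it avoids ranking healed ulcers by baseline size.
2. Report the linear regression, with a t reference, as a sensitivity analysis, and drop the z cut-off.
3. State power for the test actually named: about 78% for t or about 75% for Wilcoxon at 18 per group. Say that both are conditional on the normal model with SD 0.5.

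The cost is a change of wording and a few points of stated power. No participants need be added. If a parametric test were preferred and 80% had to be met exactly, 19 evaluable per group would mean 19 / 0.80 = 23.75, so 24 randomised per arm and 48 in total. That is not worth doing for a pilot.
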